## Abstract

**Background::**

A better understanding of how multicomponent school-based interventions work and their effects on health and education outcomes are needed. This paper described the methods of the *Movimente* Program, a school-based intervention that aims to increase physical activity (PA) and decrease sedentary behavior (SB) among Brazilian students.

**Methods::**

This is a cluster randomized controlled trial with adolescents from 7th to 9th grade in public schools from Florianopolis, Southern Brazil. After agreement, 6 schools were randomly selected to intervention or control groups (3 schools each), and all eligible students were invited to the study. The *Movimente* intervention program was performed during a school year and included 3 main components: Teacher training (including face-to-face meeting, social media platform, and handbook with lesson plans); improvements in the PA environment in school; and educational strategies. Control schools continued with their traditional schedule. Baseline (March/April 2017), postintervention (November/December 2017), and maintenance (June/July 2018) evaluations included PA and SB as primary outcomes (assessed by self-report and accelerometry). Secondary outcomes included psychosocial factors related to PA and SB (e.g., social support and self-efficacy), as well as health (e.g., quality of life and nutritional status) and education (e.g., academic achievement) outcomes. A program evaluation was performed based on the RE-AIM framework. Participants, intervention staffs, and evaluators were not blinded to group assignment, but a standardized evaluation protocol was applied independently of the trial allocation.

**Results::**

Statistical analyses will include a multilevel approach for repeated measurements and mediation analysis. Any side effects of the intervention will be recorded. The sample size close to that expected (n = 1090) was reached (n = 999). The results of this trial will involve valuable information about the effect and the evaluation of a multicomponent intervention carried out in a middle-income country.

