### Power calculation

2.2

All sample size power calculations considered a statistical power of 80% and a 5% significance level for 2-tailed tests. An odds ratio of 2^[18]^ was considered meaningful, that is, students from the intervention group would be 2 times more likely to become active (self-report measure) compared with their peers from the control group. Considering these parameters and the sample design (RCT), a minimum sample of 517 subjects (1:1 between intervention and control groups) was estimated using the software OpenEpi.^[19]^ Because of the clustered nature of the sampling frame,^[18]^ the study sample was doubled to n = 1034 schoolchildren.

When estimating a sample size for PA as a continuous variable (self-report measure) using the software GPower 3.1, a sample of 1090 students has a statistical power to identify effect size equal to or higher than 0.17 (i.e., intervention vs control differences of 200 minutes per week in PA, the primary outcome) in scores in the adjusted comparisons between control (intervention and control) versus time (baseline and follow-up), considering the effect size found in a previous study using subjective measures.

Finally, considering the sample power for mediation analyses procedures (based on a simulation study from Fritz and MacKinnon ^[20]^), the needed sample to detect small mediation effects (standardized change of 0.14 or higher) when testing the mediating role of variables (i.e., social support for PA) in the intervention effect on primary outcomes is 539 for mediation analyses using PRODCLIN and 462 subjects for Bias-corrected bootstrap methods.^[20]^

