### Recruitment of schools and participants

2.4

The study was approved by the Municipal Secretary of Education, Florianopolis and recruitment of schools occurred from October to November 2015. An invitation was sent to the 18 schools by email, asking the principal of each school if they were interested in being part of the *Movimente*, irrespective of the study condition (intervention or control). Out of 18 schools, 7 agreed to participate in the research. One school (n = 6 classes) was selected for conducting the pilot study, and 6 schools were matched (number of classes and geographic location) and randomly assigned to intervention or control arms. This matched process was adopted to avoid contamination between groups (intervention and control) and guarantee an equal distribution of schools from different geographic areas in both the groups. Also, we matched schools considering the sample size (based on the number of classes) because it varied greatly between schools (from 7 to 13 classes). The socioeconomic backgrounds and teaching schedules of these schools are the same. They were all municipal public schools, with a target audience that is very similar in terms of economic and human development index. Thus, the allocations were made to get a peer-grouped (1:1 ratio) aimed to achieve a balance between trial levels (3 schools in intervention group and 3 in control group), considering the number of classes in the schools (2 schools had between 6 and 8 classes; and 4 schools had between 9 and 11 classes).

To avoid contamination between control and intervention groups, schools were not informed about which group they were in until after baseline data collection. All students in grades 7 to 9 from the 6 selected schools who attended the first weeks of school (1427 students) were eligible to be part of the program (intervention = 796 and control group = 631). In baseline data collection, a total of 370 parents did not deliver their consent after 5 attempts to send the consent form for their children and a telephone call attempt. Fifty-eight students declined to be part of the research, and 999 adolescents (response rate = 70%) completed the baseline questionnaire (intervention group n = 580; response rate = 72.9%; control group: n = 419; response rate: 66.4%). Adolescents with mental and/or physical disabilities as well as those who did not attend the first 3 weeks of the school year (period of the collecting data) were not eligible.

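### The target of 1090 for continuous self-reported physical activity has no margin for follow-up loss, and the 999 students at baseline give about 75% power, not 80%, on the plan's own calculation

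*Protocol article*

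**What the plan says.** Section 2.2 (Power calculation) sets common parameters: "All sample size power calculations considered a statistical power of 80% and a 5% significance level for 2-tailed tests". It then gives two targets for self-reported physical activity.

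- **Binary outcome, odds ratio 2.** "a minimum sample of 517 subjects (1:1 between intervention and control groups) was estimated using the software OpenEpi". This was then inflated: "Because of the clustered nature of the sampling frame,^[18]^ the study sample was doubled to n = 1034 schoolchildren".
- **Continuous outcome.** "a sample of 1090 students has a statistical power to identify effect size equal to or higher than 0.17", where 0.17 is equated with a difference of 200 minutes per week between the arms, for a comparison over baseline and follow-up.

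Section 2.4 (Recruitment) reports what was achieved: "999 adolescents (response rate = 70%) completed the baseline questionnaire (intervention group n = 580", with 419 in the control group. Section 2.7.2 schedules two later assessments, T1 in November/December 2017 and T2 in June/July 2018. The Results part of the abstract sums up: "The sample size close to that expected (n = 1090) was reached (n = 999").

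Section 2.2 mentions no allowance for students lost between baseline and either follow-up.

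**The concern.** The size of 1090 yields 80% power only if 1090 students, equally divided, contribute to the comparison. The 999 is smaller, is unequally divided, and is counted before any loss at T1 or T2. The abstract nevertheless presents the planned size as nearly reached, without saying that 999 is a baseline count or that the arms are unequal. The limitations in the Discussion do not mention sample size.

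A reader would therefore take 80% power for a difference of 200 minutes per week as more or less secured. If the trial found no difference, that reader could treat the result as firmer evidence against such an effect than the design supports.

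**Working it through.** **Inputs.** From section 2.2: power 80%, two-sided alpha 5%, effect size d = 0.17, 0.17 equivalent to 200 minutes per week, target 1090; binary target 517 doubled to 1034. From section 2.4: 580 intervention and 419 control at baseline. The document gives no loss rate, so 10%, 20% and 30%, equal in both arms, are assumptions for illustration.

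**1. Reproduce the plan's figure.** The normal approximation is n per arm = 2(1.960 + 0.842)² / 0.17² = 543.2, rounded up to 544 (1088 in total). The exact two-sample t-test solves to 544.1, rounded up to 545 per arm, so 1090 in total, with power 80.1%. The plan's number is matched with nothing left over for attrition or for clustering.

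**2. Origin of 1034.** 2 × 517 = 1034. The whole of the doubling is attributed to clustering, so this target holds no attrition margin either.

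**3. Shortfall at baseline.** 1090 − 999 = 91 (8.3%). 1034 − 999 = 35 (3.4%). The unequal split costs a little more: 4 × 580 × 419 / 999 = 973 balanced students.

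**4. Power for d = 0.17 with the actual arms.** The non-centrality is 0.17 × √(580 × 419 / 999) = 2.65, and Φ(2.65 − 1.96) is about 0.755. The detectable effect at 80% power is solved from the same t-test and converted as d × 200 / 0.17. No design effect is applied here, as in step 1.

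| Loss (assumed) | Students | Power for 0.17 | Detectable effect | Minutes per week |
|---|---|---|---|---|
| 0% | 999 | 75.5% | 0.180 | 212 |
| 10% | 899 | 71.0% | 0.190 | 223 |
| 20% | 799 | 65.9% | 0.201 | 237 |
| 30% | 699 | 60.1% | 0.215 | 253 |

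Only the first row is free of any assumption about loss.

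**5. Same calculation with clustering.** Halving the arm sizes, which is the factor of 2 that section 2.2 applies to the binary target, gives about 46% power for 0.17 with no loss. The table in step 4 is therefore the favourable side of the picture.

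**6. The odds ratio of 2.** Section 2.2 does not state the control proportion behind 517. Without a continuity correction, a control proportion near 11% or 80% would give about 517; with one, near 12.5% or 78%. If 517 is taken at face value and 1034 is treated as giving exactly 80%, then 999 split 580/419 gives about 77.6%. If the control proportion were instead 39% (the complement of the 61% not reaching the daily activity level in section 2.3, which the plan does not name as an input), only 266 students would be needed before doubling, and 999 would give about 97% even with a design effect of 2. The answer depends on an input that is not stated.

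**The case against.** Five points can be made on the other side.

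- **The abstract sentence is not false.** It prints 1090 and 999 together, and section 2.4 reports arm sizes and refusals openly. That stands: no sum is wrong. What is missing is that 999 is a baseline count and that the stated power does not carry over to it.
- **The follow-up figures are hypothetical and use a simpler test.** This stands too. Section 2.2 speaks of adjusted comparisons, and section 2.12 plans mixed models for repeated measurements, which keep students with partial data. If 0.17 is an unadjusted standardised effect, adjustment for baseline would restore 80% at a baseline to follow-up correlation of about 0.33 with no loss, 0.44 at 10% and 0.53 at 20% (from 0.17 divided by the detectable effect, set equal to √(1 − r²)). If 0.17 is already an adjusted effect, that gain is not available. The text does not settle which. The number 1090 claims no such gain, because it equals the plain two-group size.
- **A reader might infer that 80% power fails for both targets.** The document does not support that for the odds ratio of 2, as step 6 shows. Nor is 1034 an unclustered figure: the 35-student gap is measured against a target already inflated for clustering.
- **Clustering matters more.** True: about 46% against 75.5%. That is a reason to put both into one restated figure; correcting for clustering alone would still leave the loss margin and the abstract's wording untouched.
- **An article condenses the protocol.** Silence on attrition would be weak evidence by itself. Here the derivation is published and the exact match to 1090 leaves no hidden margin. It is true that 1034 / 0.95 is about 1089, but section 2.2 derives 1090 from the 0.17 effect and states no 5% addition.

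**Conclusion.** The point holds for the continuous target. The stated 80% power for 0.17 belongs to 1090 students in equal arms with no loss; the 580 and 419 students at baseline give 75.5%, with a detectable effect of about 0.18 or 212 minutes per week. This rests only on the plan's own inputs and its own type of calculation. Any loss at T1 or T2 lowers it further for an unadjusted comparison, to about 71% at an assumed 10% and 66% at 20%, and the mixed model may recover part of that.

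Two stronger readings go beyond the document. One is that the trial will have some particular power at follow-up: neither the loss rate nor the baseline correlation is given. The other is that power for the odds ratio of 2 is shown to fall short: that cannot be verified either way. The sample sizes for mediation (539 and 462) are met by 999 at baseline.

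The gap at baseline is about 4.5 percentage points: modest in itself, but worth correcting because the abstract invites the opposite impression.

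**What to change.** No further enrolment and no change of design.

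- **Abstract, Results.** Say that 999 students (580 intervention, 419 control) completed baseline, that this is below both 1034 and 1090, and that it is before any loss to follow-up.
- **Section 2.2.** Restate the power or detectable difference for the 0.17 effect with the actual arm sizes, the observed loss at T1 and T2 or a stated range of loss, and the clustering design effect, all in the same calculation. A figure corrected only for loss would still be too favourable. If credit is taken for baseline adjustment, state the assumed correlation and whether 0.17 is an adjusted effect.
- **Section 2.2, binary target.** Give the control proportion behind 517, so that the effect of the 35-student gap can be checked.

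The cost is a reworded sentence and one recalculation. The stated power will look less favourable. A null result should in any case be read from the confidence interval for the difference in minutes per week, since a revised power figure does not change the data collected.

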**Conclusion::**

By creating opportunities for adolescents to be active at school using multicomponent strategies, the *Movimente* program has the potential to enhance students health and academic performance which may encourage the school community (e.g., teachers, principals) to adopt the program. Also, this trial will provide evidence for practitioners, policy makers, and researchers on how multicomponent program may be implemented in a school setting.

**Trial registration::**

The trial is registered at the Clinical Trial Registry (Trial ID: NCT02944318; date of registration: 18 October 2016).

## Introduction

1

The investment in adolescent health is one of the priority goals of the sustainable development proposed by the United Nations in the 2030 agenda.^[1]^ In addition, World Health Organization (WHO) recognizes that increasing physical activity (PA) and reducing sedentary behavior (SB) may prevent noncommunicable diseases and morbidities in the general population.^[2]^ It has been acknowledged that promoting a healthy lifestyle to increase the population prevalence of those reaching PA recommendations^[3]^ will improve population health.^[4]^ However, to achieve a more active and healthier society, effective strategies that make PA part of daily life are necessary.^[4]^

Promoting PA and reducing SB have been strongly encouraged in low and middle-income countries (LMICs).^[5]^ Despite PA interventions in LMICs having been nominated by experts as a research question priority,^[6]^ a systematic review of PA interventions in adolescents found that only 3.8% of the included studies came from these countries.^[7]^ Multisetting interventions (e.g., family, school)^[7]^ that identify the reasons why a program succeeds or fails to encourage adolescent PA and other obesity-related behaviors are needed.^[8]^ Schools are a key setting for promoting healthy lifestyles in youth,^[9–11]^ and a bilateral relationship between health and education has been emphasized by the World Health Organization's Health Promoting Schools (HPS) framework.^[10,12]^

This proposes a healthy school environment based on 3 main dimensions: health education included in the school curriculum; improvements in the physical and/or social school environment; and actions that engage families and/or community.^[10,12]^ A recent review of interventions based on the HPS framework showed that it is effective for improving PA in students.^[12]^ Conversely, there is a need to better articulate the connection between health and education outcomes. Systematic reviews show that among 67 included studies that used a HPS framework, 56 did not indicate any educational, and/or school-related outcomes.^[10,12]^ A better understanding of health and education outcomes and how they impact each other is needed.

In addition to using effective frameworks, it is also important to investigate the mechanisms of effectiveness of interventions on PA- and SB-related variables (e.g., perceptions of self-efficacy, social support, and environment aspects), and how these variables explain changes on PA practice or SB.^[8,13]^ van Stralen et al ^[8]^ performed a systematic review on this topic and found 18 interventions had reported on mediators of PA. However, most of the potential intrapersonal (e.g., knowledge, self-efficacy), interpersonal (e.g., social support, peer, and family model), and environmental (e.g., perception and environmental characteristics) mediators associated with PA remained largely unexplored. Evidence of intervention mediators for reducing SB among young people is even more limited.^[8,14]^ Thus, identifying the complex mechanisms by which interventions achieve behavior change is important because they can identify the critical components of the program success, contributing to the improvement of new, effective, scaled-up interventions.

Based on the gaps portrayed, the objective of this paper is to provide a step-by-step description of the design of the *Movimente* Program, a school-based PA and SB intervention aimed to increase PA and decrease time spent in SB among Brazilian student's grades 7 to 9. The intervention is based on the HPS framework, focusing attention not only on the main outcomes (PA and SB), but also on potential mediating factors and health and educational outcomes (e.g., food habits, nutritional status, quality of life, and school achievement). A mixed-method process evaluation as well as maintenance of effects will also be conducted.

## Methods

2

The program was conceptualized and designed by a research team based on previous health promotion projects in Brazil.^[15,16]^ The intervention was developed in line with the recommendations of a previous systematic review on the HPS framework.^[12]^ Guided by the *PA Evaluation Handbook*,^[17]^ the logic model of the program was developed. As recommended,^[12]^ this framework describes the program's main components as well as the interactive tools that will guide researchers throughout each step of the program (Fig. 1).

**Figure 1 F1:**
[figure not shown]
Logic model of the *Movimente* Program. PA (physical activity), SB (sedentary behavior), PE (physical education).

### Power calculation

2.2

All sample size power calculations considered a statistical power of 80% and a 5% significance level for 2-tailed tests. An odds ratio of 2^[18]^ was considered meaningful, that is, students from the intervention group would be 2 times more likely to become active (self-report measure) compared with their peers from the control group. Considering these parameters and the sample design (RCT), a minimum sample of 517 subjects (1:1 between intervention and control groups) was estimated using the software OpenEpi.^[19]^ Because of the clustered nature of the sampling frame,^[18]^ the study sample was doubled to n = 1034 schoolchildren.

When estimating a sample size for PA as a continuous variable (self-report measure) using the software GPower 3.1, a sample of 1090 students has a statistical power to identify effect size equal to or higher than 0.17 (i.e., intervention vs control differences of 200 minutes per week in PA, the primary outcome) in scores in the adjusted comparisons between control (intervention and control) versus time (baseline and follow-up), considering the effect size found in a previous study using subjective measures.

Finally, considering the sample power for mediation analyses procedures (based on a simulation study from Fritz and MacKinnon ^[20]^), the needed sample to detect small mediation effects (standardized change of 0.14 or higher) when testing the mediating role of variables (i.e., social support for PA) in the intervention effect on primary outcomes is 539 for mediation analyses using PRODCLIN and 462 subjects for Bias-corrected bootstrap methods.^[20]^

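### The target of 1090 for continuous physical activity contains no clustering allowance, although schools are randomised and the binary calculation in the same section is doubled

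*Protocol article*

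**What the plan says.** Section 2.2 (Power calculation) opens with a rule for every calculation in it: "All sample size power calculations considered a statistical power of 80% and a 5% significance level for 2-tailed tests".

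- **Binary outcome (becoming active, odds ratio 2).** "a minimum sample of 517 subjects (1:1 between intervention and control groups) was estimated using the software OpenEpi". Then, citing the clustered sampling frame, "the study sample was doubled to n = 1034 schoolchildren".
- **Continuous outcome.** The next paragraph begins "When estimating a sample size for PA as a continuous variable (self-report measure) using the software GPower 3.1" and states that "a sample of 1090 students has a statistical power to identify effect size equal to or higher than 0.17". It equates this with "intervention vs control differences of 200 minutes per week in PA, the primary outcome" and describes the contrast as being "in the adjusted comparisons between control (intervention and control) versus time (baseline and follow-up". It mentions no doubling, design effect or ICC.

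Section 2.1 makes the school the unit of randomisation, and section 2.4 gives three schools per arm. The Results paragraph of the abstract adopts the continuous-outcome figure as the trial's target: "The sample size close to that expected (n = 1090) was reached (n = 999". Section 2.4 shows that 999 is the number who completed the baseline questionnaire, 580 in the intervention arm and 419 in the control arm.

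**The concern.** Two adjacent calculations for the same school-randomised trial treat clustering differently. The binary calculation is inflated by 2 and the continuous one is not visibly inflated at all. The uninflated figure, being slightly the larger of the two, became the expected sample size in the abstract.

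If 1090 is a sample size for independent students, the stated 80% power for an effect of 0.17 does not apply to this design. A reader would then take the trial to be more sensitive than it is, both when judging the design and when weighing a result that shows no clear difference.

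**Working it through.** **Inputs from the article.** Effect size 0.17; power 80%; two-sided 5%; total 1090 (section 2.2). Inflation factor 2, from 1034/517 (section 2.2, binary outcome). Six schools; 580 and 419 students enrolled; 1427 eligible (section 2.4). **Assumed, because not given:** 1:1 allocation for the continuous calculation, the ICC, and the baseline-to-follow-up correlation r.

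**Step 1. Reproduce 1090.** For two independent means with standardised difference d, the normal approximation is n per arm = 2 × (1.960 + 0.842)² / d². With d = 0.17 this gives 544 per arm, 1088 in total. The exact noncentral-t calculation gives power 0.7999 at 544 per arm and 0.8006 at 545. The smallest adequate total is therefore 2 × 545 = 1090, an exact match with no inflation.

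Other readings do not fit:

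- One-sided test: 856.
- Paired test, or ANOVA with f = 0.17: about 274.
- Repeated-measures ANOVA with f = 0.17: 44 to 234 for correlations from 0 to 0.7.

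**Step 2. Apply the factor of 2.** The required total is 2 × 1090 = 2180, against 1427 eligible students. This holds only if the design effect stays at 2. At 1090/6 ≈ 182 students per school, a design effect of 2 corresponds to an ICC of 1/(181.7 − 1) ≈ 0.0055. Adding students within the same six schools would raise the design effect further.

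**Step 3. Power for 0.17.** SE = √[DE × (1 − r²) × (1/n₁ + 1/n₂)], and power ≈ Φ(0.17/SE − 1.96).

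| Students | DE | r | SE | 0.17/SE | Power |
|---|---|---|---|---|---|
| 545 v 545 | 1 | 0 | 0.0606 | 2.81 | 80% |
| 545 v 545 | 2 | 0 | 0.0857 | 1.98 | 51% |
| 580 v 419 | 1 | 0 | 0.0641 | 2.65 | 75.5% |
| 580 v 419 | 2 | 0 | 0.0907 | 1.87 | 47% |
| 580 v 419 | 2 | 0.5 | 0.0785 | 2.16 | 58% |
| 580 v 419 | 2 | 0.6 | 0.0725 | 2.34 | 65% |
| 580 v 419 | 2 | 0.7 | 0.0648 | 2.63 | 75% |

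Reaching 80% at design effect 2 needs r of about 0.71 at 1090, or about 0.74 at 580 v 419.

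**Step 4. Detectable effect at 999.** With design effect 2 and r = 0 it is 2.80 × 0.0907 ≈ 0.25 SD.

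**Step 5. Sensitivity.** With an assumed ICC of 0.01 at 1090, DE = 1 + 180.7 × 0.01 = 2.81 and power is about 39%. A t reference with 4 degrees of freedom for six schools, at design effect 2 and r = 0, gives about 33% at 1090 and 30% at 999.

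**The case against.** The strongest reply is that the article describes a baseline-adjusted comparison over time, and such adjustment could offset a design effect of 2. In part this stands. The 51% and 47% figures give no credit for adjustment and are one end of a range. But no correlation is stated, r = 0.5 to 0.7 still leaves power at 999 below 80%, and the exact match at design effect 1 shows no sign of such a credit in 1090.

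Three further objections also have force:

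- **The test is not named.** That 1090 came from a two-sample t-test is an inference. A repeated-measures ANOVA with f = 0.085 and zero correlation needs 546, which doubles to 1092. That variant includes a doubling, but it rests on unstated choices and misses the stated number.
- **The factor of 2 is stated only for the binary outcome.** Carrying it to continuous activity is an illustration. The article gives no ICC from which the true loss could be found.
- **The 4-df reference is not the article's.** The schools were matched before randomisation, and a pair-matched analysis would leave 2 degrees of freedom, with lower power still.

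A reader might also infer more than the document supports. Dividing 200 minutes by 0.17 implies an SD of about 1176 minutes per week, and hence a detectable difference of roughly 300 to 400 minutes. The article gives no SD, so that conversion depends on reading 0.17 as Cohen's d. Nor does the sizing gap show that the analysis ignores clustering: section 2.12 plans multilevel models. The lack of a stated attrition allowance is not an error either, since a condensed article may leave it to the full protocol.

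**Conclusion.** The point holds as an inconsistency within section 2.2. The continuous-outcome target has no stated clustering allowance, matches an unclustered calculation to the student, and is presented as giving 80% power in a trial that randomises six schools. The direction of the error is clear; its size is not fixed by the document.

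Under the illustrative design effect of 2, power for 0.17 at the enrolled 999 runs from about 47% with no baseline credit to about 75% at an assumed correlation of 0.7. A larger ICC or a few-cluster reference distribution lowers it. The shortfall at 999 does not depend on clustering alone: treating students as independent and giving no baseline credit, power is already 75.5%. The abstract's comparison therefore sets a baseline count against a target fixed before clustering.

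**What to change.** - **Section 2.2:** state that 1090 is a figure for independent students, with no clustering allowance, and name the test and any baseline correlation used.
- **Section 2.2:** restate power for 0.17, and the effect detectable with 80% power, for 999 students in six schools over a stated range of ICC (or design effect) and baseline correlation. One anchor is about 0.25 SD at design effect 2 with no baseline credit. Show a small-cluster reference distribution as a sensitivity case.
- **Abstract, Results:** qualify the comparison of 999 with 1090, saying that 999 is the baseline count and 1090 the target before clustering.

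Enrolment is complete, so the cost is a text correction. The stated power becomes less favourable; the design and the planned multilevel analysis are unchanged.
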